## Abstract

**Background:**

Forearm radial artery occlusion (RAO) is a common complication after transradial coronary procedures. Traditional patent hemostasis, relying on operator-dependent assessment, results in labor-intensive processes and inconsistent RAO rates.

**Methods:**

This is a single-center, prospective, randomized, open-label, parallel-group superiority trial. We plan to enroll 818 patients scheduled for transradial coronary angiography. Participants will be randomly assigned (1:1) to either a novel balloon pressure monitoring system (integrating high-precision digital manometry with physiologically-phased decompression) or traditional patent hemostasis. The primary outcome is the incidence of ultrasound-confirmed forearm RAO at 24 hours post-procedure. Key secondary outcomes include rates of access-site vascular complications and bleeding events, as well as objective metrics of hemostasis efficiency. Recruitment Status: Recruitment commenced in September 2024 and is ongoing; the target sample size is anticipated to be reached by May 2026. Analysis will follow the intention-to-treat principle.

**Results/ Trial Status:**

As a protocol paper, no results are reported. The trial is currently in the recruitment phase.

**Conclusions:**

This trial will provide the first large-scale randomized evidence on whether digital manometry-guided compression reduces RAO, potentially bridging the efficacy-effectiveness gap between optimized research protocols and routine practice.

**Trial registration:**

The trial was registered with the Chinese Clinical Trial Registry (ChiCTR) in August 2024, under the registration number ChiCTR2400088258.

## Introduction

### Background

Transradial access (TRA) is currently the standard vascular access site for coronary angiography and intervention, endorsed by international guidelines due to its superior safety profile over transfemoral access [1]. Advantages include significant reductions in access-site bleeding, vascular complications, and reduction of mortality, especially in higher risk patients [2], along with improved patient comfort and cost-effectiveness [1]. However, forearm radial artery occlusion (RAO) remains a common complication, with real-world incidence up to 33% [3]. This complication compromises the future utility of the artery for subsequent coronary procedures, as a surgical conduit, or for arteriovenous fistula creation [1,2].

Patent hemostasis is the cornerstone for preventing RAO [2]. Yet clinical translation is limited by inability to visualize real-time blood flow, reliance on empirical pressure titration through repeated photoplethysmography [2], and a cumbersome verification process [2]. These drawbacks hinder standardization, consume time and resources, and perpetuate the gap between protocol and practice [2]. Although adjunctive strategies (e.g., ipsilateral ulnar artery compression [4] or distal transradial approach [1,5]) can further reduce RAO, their adoption remains limited by device availability, complexity, and learning curves. An objective, standardized, easily implementable hemostasis system remains an unmet need.

Methodologically, existing evidence is fragmented: most studies are non-randomized or retrospective, with heterogeneity in compression protocols, devices, and RAO definitions [2,3,6–9]. Moreover, the predominance of single-center designs limits generalizability [8–10], further widening the efficacy–effectiveness gap and compromising external validity [11].

To address these challenges, we developed a novel balloon pressure monitoring system that integrates high-precision digital manometry with a physiologically-guided, staged decompression strategy. The present trial is designed to evaluate whether digital manometry-guided compression reduces RAO compared with traditional patent hemostasis, potentially bridging the gap between optimized research protocols and routine practice.

## Methods

### Rationale and theoretical basis

The central hypothesis of this study is grounded in the following pathophysiological principle: effective hemostasis at the radial artery puncture site requires maintaining external compression pressure within a precise “therapeutic window” [2]. The lower limit of this window is the minimum pressure needed to seal the puncture site and prevent bleeding [7], while the upper limit is the maximum pressure that does not completely block antegrade blood flow (thus avoiding blood stasis and endothelial injury) [12].

Traditional patent hemostasis, relying on subjective assessment and imprecise volume-based compression, often fails to maintain pressure within this therapeutic window [2,3]. Consistent with international consensus, RAO prevention relies on three pillars [2]: small sheath/catheter size, adequate intra-procedural anticoagulation (e.g., 6-French sheaths, weight-adjusted heparin to maintain ACT 250–300 s), and non-occlusive (“patent”) hemostasis. While the first two are easily standardized, the third remains operator-dependent, representing a key evidence-practice gap [2].

To objectively standardize this critical pillar of radial artery hemostasis, we developed a novel balloon pressure monitoring system. The present trial, a prospective randomized controlled trial conducted in accordance with the SPIRIT guidelines (S1 Checklist, SPIRIT 2025 checklist), compares the safety and efficacy of the novel system versus conventional hemostasis following transradial coronary angiography, with the primary endpoint of preventing RAO. The study timeline and flowchart are illustrated in Figs 1 and 2. The system comprises a radial artery compression balloon, a high-precision digital manometer (± 3.75 mmHg), and a pressure-modulation syringe, as shown in Fig 3. Fig 4 (left panel) outlines the standardized operational protocol for the system, which introduces two key innovations designed to overcome limitations inherent to traditional methods:

**Fig 1 pone.0350563.g001:**
[figure not shown]
SPIRIT Schedule of enrollment, intervention, and assessments of the outcomes. The schedule outlines the timing of participant enrollment, group allocation, post-procedure hemostasis interventions, and the assessment windows for primary and secondary outcomes. RAO, radial artery occlusion.

**Fig 2 pone.0350563.g002:**
[figure not shown]
Study protocol flowchart, adapted from CONSORT. The flowchart details the screening, randomization, intervention allocation, follow-up, and planned analysis populations.

**Fig 3 pone.0350563.g003:**
[figure not shown]
Structure diagram of the balloon pressure monitoring system components. The system consists of a radial artery compression balloon, a high-precision digital manometer for real-time pressure feedback, and a pressure-modulation syringe for precise pressure adjustments.

**Fig 4 pone.0350563.g004:**
[figure not shown]
Comparison of standardized operational procedures. Left panel: digital pressure monitoring system protocol. Right panel: traditional patent hemostasis protocol.

#### 1. Quantitative pressure control: From empirical volume to real-time vascular wall pressure.

The system shifts the control target from the “input volume” of air (mL) to the direct, real-time measurement of the “endpoint metric”: the actual pressure exerted on the vascular wall (mmHg). By starting from a supra-systolic safety baseline and titrating down to identify the individual’s minimum effective hemostatic pressure, it establishes a precise and reproducible benchmark. This ensures compression is consistently maintained within the individualized therapeutic window, eliminating variability introduced by differences in tissue compliance, adipose thickness, or bandage tightness.

#### 2. Physiologically phased regulation: Closed-loop management dynamically adapted to hemostasis and repair.

The system’s decompression strategy is not governed by rigid time intervals but dynamically synchronizes with the endogenous stages of vascular repair (hemostasis, inflammation, and tissue remodeling) [13], forming an adaptive closed loop (Fig 5). Following initial hemostasis, pressure is cautiously reduced to restore antegrade flow. The resulting shear stress acts as a key biomechanical signal, activating endothelial repair programs—notably by upregulating nitric oxide synthesis [12–15]. This promotes vasodilation and inhibits platelet aggregation, thereby mitigating secondary thrombosis [12–14]. Subsequent stepwise decompression further supports inflammatory clearance and re-endothelialization [14,16]. The entire process adheres to the principle of “increase pressure if bleeding occurs, decrease pressure if hemostasis is secure,” ensuring dynamic matching of compression intensity with the patient’s real-time hemostatic status.

**Fig 5 pone.0350563.g005:**
[figure not shown]
Mechanism of synchronisation with vascular repair phases. The diagram illustrates how the system’s staged decompression aligns with the three phases of vascular repair: hemostasis/thrombus stabilization (Phase A), endothelial activation/shear-stress-mediated repair (Phase B), and inflammatory clearance/remodeling (Phase C).

By integrating these innovations, the balloon pressure monitoring system aims to transform patent hemostasis from an operator-dependent art into a standardized, physiology-guided engineering process, thereby bridging the efficacy-effectiveness gap for RAO prevention.

### Study design and purpose

This is a single-center, prospective, randomized controlled trial (RCT) designed to compare the safety and efficacy of our novel system versus traditional patent hemostasis for post-coronary angiography radial artery hemostasis, with preventing forearm RAO as the primary goal. As the first large-scale RCT focusing on digital manometry-guided hemostasis for RAO prevention, this study plans to enroll 818 eligible patients, who will be randomly assigned in a 1:1 ratio to either the balloon pressure monitoring group or the traditional hemostasis group. Allocation concealment will be ensured using computer-generated random sequences and sequentially numbered, opaque sealed envelopes. To minimize bias, independent investigators assessing primary and secondary endpoints will be blinded to patient group allocations. Follow-up will continue until hospital discharge, with an optional 30-day outpatient follow-up for exploratory RAO assessment.

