#### 3. Endpoint adjudication committee.

Composition: This committee includes two vascular ultrasound specialists and one interventional cardiologist, all of whom are blinded to treatment group allocation.

Roles & Responsibilities: It independently adjudicates all primary endpoint events (24-hour radial artery occlusion) and predefined serious vascular complication endpoints (e.g., pseudoaneurysm, arteriovenous fistula). All imaging and clinical data for suspected endpoint events undergo centralized, blinded assessment by this committee based on pre-specified standardized definitions. Its adjudication is final.

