#### Blinding implementation.

Given the distinct nature of the two interventions, blinding of the operators performing hemostasis or the patients is not feasible. Therefore, to minimize assessment and measurement bias, the following blinding measures are implemented: 1) blinding of endpoint assessors, with the primary endpoint (24-hour forearm RAO) assessed by an independent, group-blinded investigator using Doppler ultrasound; and 2) blinding of data analysis, with statistical analysis conducted by an independent statistician blinded to group allocation.

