#### Unblinding procedure.

Given that the treating physicians are unblinded, emergency unblinding for clinical management is not required. However, the blinding for the endpoint assessors and statisticians will be maintained throughout the trial. In the exceptional circumstance that unblinding of a participant’s allocation is deemed necessary for the safety assessment by the DSMB or for regulatory reasons, a formal request must be submitted to and approved by the Steering Committee. The unblinding will then be performed by the independent statistician who holds the allocation list, and the date and reason will be fully documented.

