### Operator training and quality control (integrated for bias mitigation)

Given the unblinded nature of operators, rigorous training and quality control will be implemented to reduce performance and detection bias, as these measures are critical for minimizing bias from non-blinded personnel:

Operator qualifications: all staff directly performing balloon pressure monitoring or assessing hemostatic efficacy will be selected from the study team and possess the required clinical credentials and routine work experience, including interventional procedures and post-procedural care.Standardized training: before trial initiation, all relevant personnel must complete a half-day centralized training. This training will cover detailed interpretation of the study protocol and procedures; principles of the system, device calibration, and demonstration of standardized operational workflows; identification and management protocols for endpoint events (e.g., forearm RAO, bleeding, hematoma); and standardized completion of case report forms (CRFs) and data management requirements.Qualification assessment: after training, each operator must successfully complete the full operational workflow for at least three simulated or real patients under the supervision of the PI or a designated supervisor. Formal qualification is granted only after confirming that the operator can execute the protocol accurately and consistently.Ongoing quality monitoring, which will be implemented as follows:(a) Periodic review: the PI will regularly audit procedural records and data to ensure protocol adherence.(b) Adverse event review: any procedure-related adverse events will trigger team discussions and retraining if necessary.(c) Blinded assessment: the primary endpoint (24-hour RAO) will be assessed by a blinded ultrasonographer to eliminate measurement bias.(d) Protocol compliance review: an independent team led by the PI will conduct periodic blinded reviews of procedural records, with group allocation concealed, to identify and address deviations.(e) Quality control for data collection of key processes: To ensure the consistency and accuracy of the high-frequency recording for key process metrics such as “active operator time,” the following measures will be implemented: (i) a designated, trained research nurse will be held solely responsible for timestamp documentation across all cases; (ii) Validated, standardized, and user-friendly timing tools (e.g., dedicated timers or tablet applications) will be used to assist in recording the timestamps of the key operational nodes. The following predefined strategy for handling missing data has already been established in the statistical plan: if the data missing rate is < 10%, a complete-case analysis will be adopted; if the missing rate is ≥ 10%, multiple imputation will be applied in sensitivity analyzes to systematically assess the potential impact of data missingness on the primary study conclusions. (iii) Specialized training for research nurses: Nurses will receive targeted training regarding the definition of “direct hands-on tasks” (including pressure adjustment, bleeding assessment, device calibration, and data documentation related to hemostasis; excluding passive observation, waiting, or auxiliary tasks not directly involved in hemostasis). Training will include the case simulations of complex scenarios (e.g., simultaneous multi-operator activities) to ensure consistent identification of task start/end times.

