### Safety assessment and harms

#### Definition.

All adverse events (AEs) will be recorded from the time of informed consent until hospital discharge. AEs will be classified as serious (SAEs) according to ICH-GCP guidelines. Bleeding events will be defined and graded according to the Bleeding Academic Research Consortium (BARC) criteria. Vascular complications (e.g., pseudoaneurysm, arteriovenous fistula) will be diagnosed by clinical assessment and confirmed by Doppler ultrasound.

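### Blinded assessment is claimed for all secondary endpoints, but time and workload cannot be blinded and no blinded review of non-serious bleeding is described

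*Protocol article*

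**What the plan says.** The protocol article describes blinding in several places.

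- **Study design and purpose** makes the general claim: "independent investigators assessing primary and secondary endpoints will be blinded to patient group allocations".
- **Blinding implementation** lists two measures. One is a blinded statistician. The other is "blinding of endpoint assessors, with the primary endpoint (24-hour forearm RAO) assessed by an independent, group-blinded investigator using Doppler ultrasound". The same section concedes that "blinding of the operators performing hemostasis or the patients is not feasible".
- **Unblinding procedure** takes it as given that treating physicians know the allocation ("Given that the treating physicians are unblinded") and says in general terms that endpoint assessors stay blinded.
- **Operator training and quality control**, item (c), limits blinded assessment to the primary endpoint. Item (e) says that "a designated, trained research nurse will be held solely responsible for timestamp documentation across all cases", and defines the timed tasks as "including pressure adjustment, bleeding assessment, device calibration, and data documentation related to hemostasis".
- **Endpoint adjudication committee** gives the blinded committee this remit: "It independently adjudicates all primary endpoint events (24-hour radial artery occlusion) and predefined serious vascular complication endpoints". **Causality and adjudication** adds all serious adverse events and significant vascular complications.
- **Secondary endpoints** lists vascular complications, bleeding events, total hemostasis time and two operator measures (peak number and active time).
- **Definition**, under Safety assessment and harms, grades bleeding by BARC and says that vascular complications "will be diagnosed by clinical assessment and confirmed by Doppler ultrasound".

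**The concern.** The general claim tells a reader that every secondary comparison is protected against assessors who know the allocation. The operational sections do not support that for bleeding or for the efficiency measures.

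This matters because of the weight these outcomes carry. The Abstract calls vascular complications, bleeding and hemostasis efficiency key secondary outcomes. Bleeding is the natural safety counterweight to a strategy meant to avoid excessive compression. The section on distinctive design features presents active operator time as something unique to this trial, and the future research section looks ahead to lower human resource demands. The system was developed by the study team.

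A call on whether slight oozing counts as a bleed, or on when a hands-on task starts and stops, leaves room for judgement. If the person making it knows the allocation, an error could favour the system. The open-label paragraph under Study limitations covers only the opposite direction: operators performing control hemostasis unusually well, so that the benefit is underestimated.

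**Working it through.** The plan states no figure on this point, so the check sets the claim beside the procedures for each outcome.

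| Outcome | Who records or assesses it, as described | Blinded step described? |
|---|---|---|
| 24-hour RAO (primary) | Independent ultrasound assessor, then committee | Yes |
| Vascular complications | Clinical assessment, Doppler confirmation, then committee for serious or significant events | Yes, at adjudication |
| Bleeding events | Bleeding assessment is an operator's hands-on task; the person who assigns the BARC grade is not named | Only if the bleed is a serious adverse event |
| Total hemostasis time | Designated nurse, live timestamps | No, and not possible as organised |
| Peak operator number | Count of staff working simultaneously on hands-on tasks | No, and not possible as organised |
| Active operator time | Designated nurse, live start and stop times for each person | No, and not possible as organised |

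**Time and workload.** The intervention procedure uses a digital manometer, a target in mmHg and steps in mmHg. The control procedure uses millilitres of air and a two-minute manual ulnar compression with pulse oximetry. The timed tasks include pressure adjustment and device calibration. Anyone timing or counting staff on these tasks sees which arm the patient is in. The article never calls the nurse unblinded, but it follows from what the nurse has to watch.

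**Bleeding.** Both the task definition in the training section and the Secondary endpoints section list bleeding assessment among the operators' hands-on tasks. Operators cannot be blinded. The Assessment section has the access site examined during hemostasis, when the device is on the wrist, and again before discharge. Bleeding is listed separately from vascular complications under both Secondary endpoints and Definition, so the committee's vascular remit does not cover it. It reaches the committee only through the serious adverse event route.

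**Count.** There are five secondary measures: vascular complications, bleeding, total hemostasis time, peak operator number and active operator time. Three of the five cannot be blinded. One (bleeding) has no described blinded review unless serious. One (vascular complications) has blinded adjudication of its serious or significant events.

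**Other checks that might fill the gap.** The blinded review of procedural records in item (d) of the training section looks for protocol deviations. It does not assess endpoints.

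**The case against.** The strongest defence has four parts.

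1. **Secondary results are not confirmatory.** The section on analysis of the primary and secondary endpoints reserves inference for the primary endpoint and warns against reading secondary results as proof of efficacy or safety. This stands, and it limits the consequence. It does not make an inaccurate blinding statement accurate: exploratory status deals with inference and multiplicity, not with how data are recorded.

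2. **Blinded grading of bleeding may exist.** A reader might infer that every non-serious bleed is graded by open-label staff alone. The documents do not say so. Detecting and managing a bleed is not the same as assigning its BARC grade, no section names the grader, and a blinded pre-discharge examination is possible. The supported statement is that blinded assessment of bleeding is claimed but not described, while detection during compression is open-label.

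3. **Vascular complications are protected.** A reader might infer that pseudoaneurysm and fistula will be looked for unevenly, because suspicion starts with unblinded clinicians. The article does not show this. It requires active questioning and access-site examination at predefined times with no difference by arm, Doppler confirmation, and final blinded adjudication of the serious or significant events. Some suspicion bias remains conceivable, but nothing in the text demonstrates it.

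4. **Recording is standardised.** One trained nurse, validated timers, a list of counted and excluded tasks and simulation training narrow the room for discretion, and the training section names detection bias as something these measures should reduce. They do narrow it. They blind nobody.

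**Conclusion.** The general blinding statement is broader than the procedures support and should be corrected. For total hemostasis time, peak operator number and active operator time, the claimed blinding cannot exist as the trial is organised. For bleeding, detection during hemostasis is open-label and blinded review is described only for serious adverse events. Serious or significant vascular complications and 24-hour RAO do have a described blinded step.

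The conclusion rests on two readings: that someone timing or counting live tasks with visibly different devices knows the arm, and that bleeding is a category separate from the committee's vascular events. The article supports both.

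The effect on results cannot be sized. The documents give no bleeding rate and no rate of missed or misclassified bleeds, so any percentage would rest on invented inputs, and the direction of any bias is possible rather than shown. A reader might also infer that the primary comparison is compromised. It is not: its ultrasound assessment and adjudication are blinded. What changes is how far the bleeding and efficiency comparisons can be relied on. This should be corrected, but it does not threaten the trial's main conclusion.

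**What to change.** 1. **Correct the text.** Under Study design and purpose, limit the blinding statement to 24-hour RAO and committee-adjudicated events. State that hemostasis time, operator workload and bedside detection of bleeding are open-label. In the open-label paragraph of Study limitations, add possible detection bias in favour of the system beside the bias against it already discussed. This costs only wording; the stated blinding becomes less favourable.

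2. **Grade recorded bleeds blind.** Have the existing blinded committee assign the BARC grade of recorded bleeding events from narratives with device, mmHg and mL details removed. The cost is preparing the narratives and a small extra workload for the committee. Bleeds already recorded since September 2024 can be included if their records hold enough detail. This protects grading only. It cannot recover bleeds that were not detected or not recorded, and the report should say so.

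Adding pseudoaneurysm and fistula fields to the 24-hour scan is not recommended. It would count clinically silent findings, contrary to the current definition, and would change ascertainment during recruitment. It would also assume a scan scope that the Primary endpoint section, which specifies only anterograde flow in the distal radial artery, does not state.

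The recommended changes leave treatment, sample size and the primary analysis untouched.
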